## Abstract

**Background:**

Latest research demonstrates a significant improvement in stress-related symptoms in psychological disorders as a result of exercise training (ET). Controlled clinical trials further validate the significance of ET by demonstrating lower salivary cortisol levels in patients with post-traumatic stress disorder (PTSD) after intervention. A significant change in cortisol and dehydroepiandrosterone (DHEA) levels can already be found after an 8–12-week ET program. The proposed study aims to investigate the impact of an 8-week ET on PTSD symptoms and changes in cortisol levels in a juvenile refugee sample from the Democratic Republic of the Congo (DRC) at an Ugandan refugee settlement. It is the first to implement an ET intervention in a resource-poor, post-conflict setting.

**Methods/design:**

In a randomized controlled trial, 198 adolescent participants aged 13–16 years from the DRC who, suffer from PTSD, will be investigated. The participants are based at the Nakivale refugee settlement, an official refugee camp in Uganda, Africa, which is among the largest in the world. The participants will be randomized into an *Exercise Training (ET) group* with a maximum heart rate (HR_max_) of > 60%, an *Alternative Intervention (AI) group* with low-level exercises, and a *Waiting-list Control (WC) group*. After the 8-week interventional phase, changes in cortisol awakening response (CAR) and DHEA in the ET group that correspond to an improvement in PTSD symptoms are expected that remain at follow-up after 3 months.

**Discussion:**

To date, there is no controlled and reliable longitudinal study examining the effects of an ET program on symptom severity in individuals with PTSD that can be explained with a harmonization of cortisol secretion. The presented study design introduces an intervention that can be implemented with little expenditure. It aims to provide a promising low-threshold and cost-effective treatment approach for the application in resource-poor settings.

**Trial registration:**

German Trials Register, ID: DRKS00014280. Registered prospectively on 15 March 2018.

**Electronic supplementary material:**

The online version of this article (10.1186/s13063-018-2753-x) contains supplementary material, which is available to authorized users.

## Background

With more than 22.5 million refugees worldwide and over 65 million people being forcibly displaced [1], the provision of health services to these populations is among the world’s most significant and challenging endeavors. These numbers are even more alarming when one considers that nine of the top ten hosting countries are not Western countries but mostly low- and middle-income countries [1]. As most of these refugees have had to flee from violent crises and have been exposed to a number of stressful and traumatic experiences, not only in their home countries but also during their flight, millions of them suffer from trauma-related mental health problems, in particular post-traumatic stress disorder (PTSD) [2]. Generally, youth in conflict zones are at risk of developing mental disorders related to their exposure to continuous and traumatic stress, which includes symptoms summarized under the diagnosis of PTSD [3]. Thus, the need for wide-scale, trauma-focused interventions is massively important to restoring refugees’ mental health. The resources that are given, however, are often found to be very low [4] and are particularly scarce for children and adolescents. Therefore, effective steps are required to alleviate the immense human and social costs [5]. Even if psychotherapeutic interventions would be capable of reducing trauma-related suffering [6], most low- and middle-income countries lack a substantial mental health system. Moreover, even if it has been proven that the training of lay counselors and local health workers can be an effective method [7], most professional psychotherapeutic interventions are resource-demanding as they require the application in one-to-one settings [8]. Besides a lack of resources, stigmatization is another big issue for various countries around the world and constitutes another barrier to mental health services, thus contributing to social isolation, distress, and difficulties in the lives of the affected people [9]. The present research initiative, therefore, focuses on Exercise Training (ET) as a promising way to administer cost-effective and low-threshold group-intervention approaches. It will be administered in a refugee settlement in Uganda, a low-income country that is currently the world’s number-eight host country for refugees escaping violent crises in neighboring countries, in particular the Democratic Republic of the Congo (DRC) [1].

### The impact of Exercise Training (ET) on stress-related mental health problems

Exercise Training (ET) has been shown to reduce an individual’s perception of stress and to improve overall mental health [10]. It is thereby important to demarcate exercise from *physical activity*. Both activities can involve large muscle groups that result in substantial increases in heart rate and energy expenditure. The most significant difference between the two is that exercise is planned and structured while physical activity is not [11]. Both can be distinguished as acute and chronic. *Acute exercise* is the physiological response to a single bout of exercise, while *chronic exercise*, which can also be called exercise *training*, refers to the repeated performance of acute exercise [11].

There are several studies describing chronic exercise as a useful intervention for PTSD patients to reduce trauma-related symptoms [12–14]. After implementing an ET program, Fetzner and Asmundson [14] found significantly reduced PTSD symptoms, with 88.9% of the participants reporting a clinically significant improvement. Furthermore, previous research has shown significantly higher reductions in PTSD, depression, anxiety, and stress-symptom severity in PTSD patients who committed to ET, compared to controls [12, 13]. According to a meta-analysis of Rosenbaum et al. [15], who investigated four intervention studies, a higher physical activity was related to less frequent and less-severe PTSD symptoms. Two of these programs used combined aerobic exercises [12, 13], whereas the other two used yoga sessions [16, 17] in their program.

### The glucocorticoid system as a potential target for the beneficial effects of ET

Exercise is a very effective stimulator of the hypothalamic-pituitary-adrenal (HPA) axis [18]. The hypothalamus produces the corticotropin-releasing hormone (CRH) which stimulates the pituitary gland which in turn releases the adrenocorticotropic hormone (ACTH) [19]. ACTH stimulates the adrenal glands to release cortisol and dehydroepiandrosterone (DHEA). DHEA and its sulfate form, dehydroepiandrosterone sulfate (DHEAS), have been found to possess anabolic properties [20], whereas high cortisol has catabolic properties [21]. Furthermore, DHEA/S has neuroprotective and anti-glucocorticoid effects [22]. Under normal conditions DHEA levels are closely correlated with cortisol; however, an imbalance of cortisol/DHEA secretion may occur when an individual experiences chronic stress [23]. Cortisol and DHEA are often addressed as a ratio that represents the balance between anabolic and catabolic hormones [24]. Budde et al. [25] found an increase in cortisol levels due to acute exercise in adolescents. According to Hill et al. [26], the exercise intensity necessary to provoke a significant increase in circulation cortisol is 60% maximum rate of oxygen consumption (VO_2max_), which shows an increase of + 39.9% in circulating cortisol levels. In general, untrained participants had lower VO_2max_ levels, significantly higher responses to cortisol post exercise, and lower hair-cortisol levels compared to participants who exercised regularly [27–29]. In regard to the chronic effects of exercise, it turned out that a higher training volume (measured in kilometers run per week) was associated with an increase in cortisol levels in young healthy men [29]. After ET, a decrease [30] as well as an increase [31] in cortisol levels was found. A distinct rise in cortisol has been observed also immediately after waking, typically peaking 30–45 min after waking [32], and has been appropriately termed the cortisol awakening response (CAR). This response is a neuroendocrine manifestation of the hypothalamic-pituitary-adrenal axis (HPA-axis) has been demonstrated to be sensitive to stressors like exercise. Although normative ranges have been developed for several populations [33], it is still unclear what may constitute a “healthy” cortisol response, as both elevated and depressed responses have been related to dysfunctional psychosocial health status [34]. Compared to adults, fewer data are available on hormone responses to exercise in children and adolescents. Regarding the HPA response to the physical activity status in adolescents, cross-sectional findings revealed no significant changes [35]. However, after presenting an acute exercise-related stressor, young individuals at early stages of puberty showed higher cortisol increases and lower DHEAS-to-cortisol ratios than late pubertal participants [36].

### The significance of glucocorticoids in PTSD

In various studies, alterations in the function of the glucocorticoid system have also been reported for PTSD patients. It is commonly accepted that PTSD patients can have a dysfunction in the HPA-axis [37]. Results on differences in baseline cortisol levels between individuals with PTSD and controls are inconsistent, depending on the research paradigm [38]. Several researchers found reduced basal cortisol levels in PTSD patients compared to healthy controls [39, 40]. In addition, cortisol levels turned out to be a significant predictor for PTSD symptoms 6 weeks and 6 months after the traumatic event [39]. At some time points, even higher cortisol levels were found in participants who had PTSD [41]. Similarly, equivocal results exist surrounding the DHEA response, in particular due to the smaller number of systematic studies in this field. Interestingly, there were negative associations between hair-cortisol levels and the number of different lifetime traumatic events, the frequency of traumatization, and the time interval since traumatization [40]. Regarding the cortisol levels of adolescents and children with PTSD, research reports an increase in cortisol concentration in PTSD victims [42]. Some other studies did not find any significant differences in cortisol levels in this age group [43] or even an attenuation in the CAR [44].

Thus, even if cortisol and DHEA are associated with PTSD and provide promising targets for the detection of changes in HPA functioning, functional consequences related to the development of stress-related psychopathologies will have to be investigated in a subsequent step, constituting a future research avenue. However, the latest studies have demonstrated the usefulness of the present research approach to utilize stress hormones as an objective marker to validate the effectiveness of ET.

Kim and colleagues [45] showed a design that is comparable to the present study by demonstrating significant changes in cortisol levels and also an improvement of PTSD symptom severity after the adult participants completed an 8-week ET program. In their study, “*Mindfulness-based Stretching”* and *“Deep Breath Exercises”* were used as low-intensity chronic exercise interventions. However, the intensity of ET had positive effects on the improvement of PTSD symptoms [12–14].

Even if a few studies suggest ET to be beneficial for children and adolescents with PTSD, no randomized controlled trial (RCT) has been reported yet that directly compares the effects of a cardiovascular condition to a sham condition in a longitudinal design. To our knowledge, there is neither a study investigating the relationship between a chronic exercise intervention and the cortisol response in young PTSD victims, nor has it ever been tested in a resource-poor, post-conflict setting.

### Study aims

The purpose of this paper is to introduce a study protocol for a RCT that aims to systematically investigate the impact of ET on PTSD symptoms and associated cortisol levels in adolescents. It is hypothesized that ET in adolescents not only leads to a sustainable decrease in PTSD symptoms in comparison to two control conditions (H1) but that the changes in PTSD symptoms also correspond to changes in cortisol (H2) and DHEA levels (H3) as markers for beneficial alterations in HPA-axis functioning. Furthermore, we expect differences in PTSD symptom severity and cortisol/DHEA ratios between participants who are highly physically active and those who are less physically active at baseline (t_1_) (H4).

## Methods/design

### Participants

This study investigates juvenile trauma victims from the Democratic Republic of the Congo (DRC), aged 13–16 years, who are based at the Nakivale refugee settlement, an official refugee camp in Uganda, Africa, which is among the largest refugee camps in the world. The government of Uganda and its United Nations High Commissioner for Refugees (UNHCR) partners provide general health services to the refugees in the settlement with few psychotherapeutic interventions. Therefore, Ainamani, Elbert, Olema, and Hecker [46] propose the ample provision of trauma-focused treatment options particularly in these settings in order to support not only individual traumatized refugees but also their families and the whole community. All participants will have a history of traumatic experiences. Participants eligible for inclusion in the intervention only involve individuals with a diagnosis of PTSD according to the *Diagnostic and Statistical Manual of Mental Disorders* (DSM-V). Exclusion criteria cover (1) acute suicidality, acute intoxication, or psychotic symptoms, (2) inability of the parent or legal guardian to provide consent, or (3) child protection issues (e.g., acute maltreatment) that are identified during the initial cross-sectional assessment and are judged by a clinician to make trial inclusion inappropriate. Additionally, the participants may not be part of any other psychological therapy or take any medication with psychoactive drugs until the study is completed. We further control for an unchanged physical activity level during the intervention.

A prior sample size calculation was performed using g*power 3 [47] based on (1) an expected medium effect size in the overall model according to cortisol and PTSD changes reported in previous studies [45], (2) the PTSD symptom severity, the trauma load and the number of potential stressors occurring during the intervention as covariates, and (3) the number of time points. The desired statistical power level was set at 0.95. The sample size calculation was corrected for an estimated dropout rate of 20%, according to other intervention studies that have already been performed in the Nakivale refugee settlement [48]. According to the power analysis, 159 participants are sufficient so that a total sample size of 198 participants is targeted to acknowledge potential dropouts.

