**Fig. 1 Fig1:**
[figure not shown]
Participant flow diagram

To assess the impact of chronic exercise on PTSD symptoms and cortisol profiles, repeated measurements with *time* (baseline (t_1_), interim test (t_1b_), post test (t_2_), 3-month follow-up (t_3_), and 6-month follow-up (t_4_)) as the within-subject factor will be conducted on the primary outcome measures *PTSD symptom severity* and awakening *cortisol profiles*. At eligibility (t_0_), the diagnosis will be verified and co-morbid diseases will be identified. In addition, at baseline (t_1_), the PTSD symptom severity, relevant information about the participants’ trauma and flight history, as well as their exposure to early life adversities will be assessed. As physiological measures, cortisol and DHEA levels will be determined. The assignment of participants to one of the three groups will be conducted afterwards. An interim measuring time point (t_1b_) at 4 weeks after the respective intervention will serve to adjust the training to the individual participant’s progress in the two exercise groups in order to assure that the ET stays over 60% HR_max_ after the 8-week interventional phase at the post test (t_2_). The baseline measures will be repeatedly assessed at the post test as well as the two follow-up measuring points (t_3_ and t_4_; see Fig. 2 and Additional file 1).

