### Interventions

#### Exercise Training (ET) group

The participants in the ET group will attend three exercise sessions every week for a total number of 8 weeks. That makes this training a chronic exercise intervention [11]. Every unit takes 45 min. Two local and experienced trainers from Uganda instruct identical classes of 25–35 participants. Each session will be performed with high intensity with a HR_max_ of 70–85%. In our preliminary work, significant cortisol and testosterone increases were found by implementing an acute exercise of 70–85% HR_max_, but not with 50–65% HR_max_ [24]. The training program will focus on improvement of cardiovascular fitness through running and running-based games of moderate to vigorous intensity (recorded on three occasions by F1 Polar HR monitors; Polar, Kempele, Finland) [49].

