#### Waiting-list Control (WC) group

No specific intervention will be implemented. However, the ET intervention will be done with this group after the end of the measurement (t_4_).

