### Measures

#### Screening

The *UCLA Child/Adolescent PTSD Reaction Index for DSM-5* (UCLA; [52]) is a screening tool recommended by the National Centre for PTSD to collect data about the kind of traumatic happening the participants experienced. It is a 24-item questionnaire assessed to DSM-V criteria for PTSD.

The *Mini International Neuropsychiatric Interview - Kid 7.0.2* (M.I.N.I.; [53]) represents a shortened psychiatric interview on the basis of DSM-V in order to help clinicians diagnose and evaluate the major psychiatric disorders. The test takes about 15–20 min and is performed in form of a standardized interview. The M.I.N.I. will help to identify acute co-morbid diseases relevant for eligibility of the participants.

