#### Hormonal analysis

The determination of the cortisol awakening response (CAR) will take place in following six samples:Sample 1 “awakening” in the morning as soon as the participants wake upSample 2 “post-awakening I” 30 min after taking the awakening sampleSample 3 “post-awakening II” 45 min after taking the awakening sample.Sample 4 “post-awakening III” 60 min after taking the awakening sampleSample 5 “post-awakening IV” at 9 a.m., collected in the schoolSample 6 “post-awakening V” at 11 a.m., collected in the school

Additionally, DHEA levels will be obtained at sample 1, sample 2, and sample 3 only. The samples will be independently collected in salivates by the participants. Saliva will be collected by either passive drooling into the tube or by chewing (for 2 min) the cotton provided with each tube. Participants must wait at least 10 min after smoking, consuming any food or drink, or teeth-brushing before collecting the saliva sample. Previous research has found different stimulation of salivary samples in children with chronic malnutrition [59]. Therefore, our implemented WC group provides the advantage of having a comparable outcome among traumatized children without any treatment condition. In addition, to control the possible influence of malnutrition onto hormonal samples, the Body Mass Index (BMI) and the skinfold thickness will be determined. Tubes will be labeled with patient identifier and returned to the laboratory via collection by the researcher. Upon arrival at the laboratory, tubes with saliva will be centrifuged to remove the upper salivary layer for subsequent measurement of cortisol and DHEA. The DHEA-to-cortisol ratio will be determined by dividing DHEA levels by the respective cortisol levels. The subjects will be informed that the sample has to be collected ± 5 min according to the respective agreed time point. Free cortisol levels in saliva will be measured using a commercially available chemiluminescence assay (IBL, Hamburg, Germany). The evaluation is carried out by [name] in Dresden, Germany.

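### The printed entry criteria and screening contain no physical or nutritional criterion, although participants run a shuttle test to failure and the ET arm trains at 70–85% of maximal heart rate

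*Protocol article*

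**What the plan says.** **Entry.** The Participants section requires a PTSD diagnosis and then lists the exclusions: "Exclusion criteria cover (1) acute suicidality, acute intoxication, or psychotic symptoms, (2) inability of the parent or legal guardian to provide consent", followed by child protection issues that a clinician judges to make inclusion inappropriate. It also bars concurrent psychological therapy and psychoactive medication.

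**Screening.** Initial procedure names three things to screen: PTSD severity, exclusion criteria (suicidality and psychotic symptoms are singled out), and child protection. Study design adds that co-morbid diseases are identified at eligibility. The only instrument named for that is in the Screening section: "The M.I.N.I. will help to identify acute co-morbid diseases relevant for eligibility of the participants". The M.I.N.I. is a psychiatric interview.

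**Exertion.** Physical performance measures describes a 20 m shuttle run that starts at 8 km/h, rises by 0.5 km/h each minute and stops when the line is missed twice running. For the ET arm, the Exercise Training section says "Each session will be performed with high intensity with a HR_max_ of 70–85"%, through "running and running-based games of moderate to vigorous intensity", in three 45-minute sessions a week for 8 weeks. Study design gives the intensity as 60–80% instead.

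**Nutrition.** Hormonal analysis says that "to control the possible influence of malnutrition onto hormonal samples, the Body Mass Index (BMI) and the skinfold thickness will be determined". The section on protection against bias lists massive weight loss, malnutrition and being overwhelmed by the intervention among the reasons to unblind.

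**The concern.** The article recognises that malnutrition may be present in this population and treats it as serious enough to break the blind, but uses it nowhere to decide who enters. An adolescent who is already malnourished at baseline would satisfy the printed entry criteria and could meet an unblinding trigger from the first day. The same gap holds for a known cardiac, respiratory or other contraindication: nothing printed asks about it.

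What is at stake is the safety of minors who are asked to run to failure and, in one arm, to train repeatedly at high intensity. The printed safeguards either act after exposure or depend on a problem being noticed by interviewers who are given no physical criterion to apply.

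**Working it through.** The check is mainly a reading of each place where a physical entry rule could stand.

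| Section | What it provides | Physical or nutritional entry rule? |
|---|---|---|
| Participants | Psychiatric state, intoxication, consent, child protection, other therapy, psychoactive drugs | No |
| Study design | Co-morbid diseases identified at eligibility | None stated; no medical instrument named |
| Screening | PTSD index and M.I.N.I. | No; both are psychological |
| Initial procedure | Three screening items; second check-up and referral for problems that are noticed | No threshold and no exclusion rule |
| Hormonal analysis; Physical performance measures | BMI and skinfold measured | No; used for hormone control and description |
| Methods to protect against sources of bias | Weight loss, malnutrition, being overwhelmed | No; reasons to unblind, so they act after allocation |
| Ethics approval | Referrals and serious-adverse-event reporting | No |

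**Planned exposure** (inputs from the Exercise Training section and the target of 198 in Participants):

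- Sessions: 3 per week × 8 weeks = 24.
- Time: 24 × 45 min = 1,080 min = 18 h per ET participant.
- ET arm size, assuming an even split because the ratio is not stated: 198 / 3 = 66, which is 33% of the sample.
- Total at full attendance: 66 × 18 h = 1,188 participant-hours.
- Shuttle run: described for participants without limit to one arm, so up to 198.

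These figures describe exposure. They do not measure harm, and the document gives no share of unsuited adolescents from which harm could be estimated.

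**BMI formula.** This matters only because the fix uses BMI. Physical performance measures prints weight divided by height. For an assumed adolescent of 40 kg and 1.60 m, that gives 40 / 1.60 = 25.0. With height squared it gives 40 / 2.56 = 15.6. Only the second can be read against a BMI-for-age cut-off.

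**The case against.** The strongest objection is that this is an absence in a condensed article. A health questionnaire or medical clearance could sit in the full protocol or the ethics file. The wording that introduces the exclusions does not claim completeness, and the screening description singles out examples. The flow diagram, the table of measures and Additional file 1 are not visible. This stands as a limit on the claim: a reader might infer that the trial has no medical check at all, and the document does not support that. It does not remove the point, because the article chose to print its eligibility list and screening steps in some detail, and anyone following them would not turn away an unsuited adolescent.

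Second, the safeguards can be read more generously. Co-morbid diseases are not limited to psychiatric ones, and the M.I.N.I. is said only to help identify them, so treating it as the sole tool is an inference. Risks are explained before consent, when a guardian could mention a known condition. The second check-up is not limited to mental health. Training is adjusted at 4 weeks, and heart rate is recorded on three occasions. All of this is fair, but none of it tells the team what to ask or whom to exclude. The adjustment is there to keep intensity above 60% of maximum, and the screening interviews are run by psychology students.

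Third, excluding malnourished adolescents narrows the target population. That is a real cost and is counted below.

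**Conclusion.** The point holds for the printed list and the described screening: they state no physical or nutritional entry criterion, while the plan includes a shuttle run to failure and, for the ET arm, 18 hours per participant of moderate-to-vigorous running-based training. It should be corrected before recruitment.

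Its size is bounded by what the document shows. Up to 198 adolescents do the shuttle run, and about 66 train in the ET arm if the split is even. A reader might go further and infer that a known number of unsuited adolescents would be enrolled, or that power or the analysis suffers. The document supports neither: it gives no prevalence of contraindications or severe malnutrition, and no sample-size or analysis figure changes. The conclusion rests on the visible text and would reduce to a request for one clarifying sentence if an unshown file already contains a medical-fitness criterion.

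**What to change.** If the full protocol already sets such a criterion, state it in the Participants section. Otherwise add a fourth exclusion: *(4) a known medical contraindication to vigorous exercise, or severe malnutrition, defined as BMI-for-age below a named cut-off fixed before recruitment.* The sponsor must choose the reference and the cut-off, since the document gives no basis for one.

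- Apply it identically to all participants, before the first shuttle run and before randomisation, so that the three arms stay comparable. Study design already places allocation after the baseline measures: "The assignment of participants to one of the three groups will be conducted afterwards". The timing of the shuttle run and of BMI is not visible in the text and should be checked against the table of measures.
- Use a few scripted health questions in the existing screening interview and the BMI already planned, computed as kilograms divided by the square of height in metres.
- Send doubtful cases through the existing second check-up and referral route, for example to the government and UNHCR partners who "provide general health services to the refugees in the settlement". No physician is then needed for every participant.

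**Cost.** One line in the eligibility list and slightly longer screening. At an assumed 5 minutes each, 198 × 5 = 990 min = 16.5 h if asked only of those otherwise eligible, plus the time to screen replacements. The number excluded is expected to be small but cannot be quantified from the document. Households are sampled until the target is reached, so exclusions would be replaced and need not reduce the sample. The results would apply slightly less to the most malnourished. Trial status reports that recruitment has not begun, so the change can still be made for every participant.
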